### Recruitment {15}

To identify potential participants and to encourage registration, the project is broadly advertised through display of flyers, posters, and bulletins in electronic or print media. Ethics-approved promotional material state that people with HCV who participate may be eligible for a payment if they commence DAA therapy. Promotional materials include the URL and/or a QR code for the project website. Following engagement and discussions with the relevant stakeholders, the promotional material is displayed on public or electronic notice boards in primary care health services, community services, organisations providing needle and syringe programs, alcohol and drug services and prison re-integration programs, mobile point-of-care HCV testing sites, and at peer-based support organisations. Primary care clinicians are informed of the project via advertisements through professional networks and contacts, including primary health networks. Selective media buying may also be used to gain more public exposure to the project.

## Assignment of interventions: allocation

### Sequence generation {16a}

Participant randomisation uses an implementation of the mass weighted urn design [14] which produces a random sequence that targets an allocation ratio based on configurable weights. Equal allocation is used until the first analysis after which the allocation weights are updated based on the joint posterior from the primary analysis model. The weights are computed as:$${w}_{k}\propto \sqrt{\frac{{\rho }_{k}{\phi }_{k}{\sigma }_{k}^{2}}{{n}_{k}+ 1}}$$for $$k>1$$(the AUD 0 dose has fixed allocation throughout) and where:$$k$$ corresponds to the dose index (AUD 0 being 1, AUD 1000 being 21)$${\rho }_{k}$$ corresponds to the probability of effectiveness (i.e. $$\ge$$ MED threshold of 0.95)$${\phi }_{k}$$ corresponds to the first difference in the probability of response at, namely $${\phi }_{k}={p}_{k}-{p}_{k-1}$$ where $${p}_{k}$$ corresponds to the posterior probability of response under arm $$k$$$${n}_{k}$$ is the number of enrolments reaching the primary endpoint for arm $$k$$

Once the weights are computed, they are normalised to unity. There are no further planned restriction or stratification with the participant randomisation.

Prescriber co-incentive randomisation is based on a pre-generated sequence using permuted blocks with a range of block sizes and with 1:1 allocation to a co-incentive and no co-incentive.

### Concealment mechanism {16b}

The allocation mechanism for participants is concealed from all parties as the sequence generation is dynamic and initiated by the participant at the time of registration. The allocation sequence for nominated preferred prescribers is pre-generated and held on a secure server accessible only by the study statistician and the software administrators of the MOTIVATE-C management system.

### Implementation {16c}

The randomisation and allocation processes are coordinated by the MOTIVATE-C management system, which is a microservices application developed by the Health and Clinical Analytics team at the University of Sydney. The system is hosted by University of Sydney with secure access, full audit trial and redundancy. Randomisation functionality is contained within a dedicated service which exposes a RESTful API that can be called by other services within the MOTIVATE-C management system. The mass weighted urn design of the randomisation service produces a random sequence that targets an allocation ratio based on configurable weights. The approach facilitates the implementation of response-adaptive randomisation without major divergence from the specified allocation ratio, which is a problem commonly experienced under response-adaptive randomisation when using simple random sampling.

Registrants initiate their own randomised allocation via the SMS interaction under the previously described response-adaptive allocation scheme. The registrant’s mobile phone number is used to confirm that they are a unique person for the project and not previously registered. If confirmed to be a new registrant, a computer-generated randomised incentive is assigned to the registrant, and they are notified of this by text message. The randomised incentive value is associated with the registrant’s phone number used for the registration. Therefore, if a registrant does not proceed to enrolment after being randomised and then tries to re-register using the phone number used previously for registration, the registrant will not be re-randomised but will be re-notified of their previously assigned incentive.

Prescriber co-incentive allocations are initiated by the navigator via the navigator portal, another component of the MOTIVATE-C management system, only if the participant nominates a preferred prescriber. Again, the implementation of the randomisation sequence is encapsulated within the randomisation microservice, but for prescriber co-incentives, the sequence is simply taken sequentially from pre-generated permuted block randomised sequences with 1:1 allocation to co-incentive or no co-incentive.

In both scenarios, the assigned treatment values are pushed to a dedicated REDCap database, which is used to retain all trial data.

## Assignment of interventions: blinding

### Who will be blinded {17a}

Participants are unblinded to the intervention as the primary research question is predicated on their knowledge of the assigned incentive value (dose). Similarly, nominated preferred prescribers are unblinded as the secondary research question is again predicated on the prescriber’s knowledge of the co-incentive value. While treatment navigators are not aware of the registrant’s assignment prior to making contact, in most cases they become unblinded due to the extent of their interaction with the participant. Prescribers may also become aware of the value of any incentive assigned to a participant they treat if the participant volunteers this information.

The study statistician needs to access participant level data for the purposes of conducting analyses and budget tracking and is therefore also unblinded. Other operational staff are not privy to the individual assigned incentive amounts but will be aware of the number of enrolled participants and aggregated summaries of the total budget expended on incentives and compensatory payments.

### Procedure for unblinding if needed {17b}

N/A. The study is unblinded.

## Data collection and management

### Plans for assessment and collection of outcomes {18a}

Only the minimum data necessary to achieve the study objectives are collected on participants (see Table 2). The rationale for this minimalism stems from our knowledge that many people HCV are socially marginalised and subject to stigmatisation, discrimination, legal issues, and other negative social and structural determinants of health. Accordingly, many people with HCV are wary of intervention programmes and are resistant to having their personal information collected. The study-relevant participant information will be recorded/documented by the navigator on the online navigator portal.

**Table 2 Tab2:** Participant demographic and clinical variables collected for the study and the timepoint of data collection

Variable	Justification/comments	Timepoint
**Registrants and enrolled participants**		
Phone number		At registration
Date of registration in the study,* i.e. the date that the participant gets randomised and is advised of the assigned incentive*	To track compliance with project timelines	
Prior treatment/current treatment for HCV	To determine eligibility	At the initial meeting with the navigator
Do you have a Medicare card		
HCV positive PCR test in the last 4 weeks		
**Enrolled participants only**		
Name	For participant identification and validation of evidence of testing/prescription/SVR	At the initial meeting with the navigator
Date of birth	To permit adequate description of the study population and validation of evidence of testing/prescription/SVR	
Sex		
Mailing address	Only if participant requests for a hardcopy of the PIS and/or physical gift card to be delivered	
Date of enrolment in the study, *i.e. the date that the participant provides verbal consent to the navigator*	To track compliance with project timelines	At the initial or follow-up meeting (if participant require more time) with the navigator
Date and results of the HCV test	Secondary endpoint and to trigger compensation payment and to track compliance with project timelines	At the navigator-participant meeting to demonstrate evidence of HCV test
Name of the nominated treatment prescriber (including name of the practice)	To enable provision of the compensation payment	At the navigator-participant meeting to demonstrate evidence of DAA prescription
Date of treatment initiation	Primary endpoint and to trigger incentive payment and to track compliance with project timelines	
Adverse events (any untoward health-related events including medical attendance or hospitalisation)	For safety monitoring	At the navigator-participant meeting 2–4 weeks following initiation of treatment
Self-reported number of scheduled/recommended doses of DAA not taken grouped into:	Secondary endpoint	28 days following completion of treatment
• < 7 days,		
• 7–13 days,		
• 14–20 days,		
• 21–27 days,		
• 28 + days		
Date and results of the SVR test	Secondary endpoint and to trigger final compensation payment	4–24 weeks following completion of treatment

### Plans to promote participant retention and complete follow-up {18b}

The treatment navigators will foster a positive relationship with the participants by providing support, including facilitation of appointments if requested, sending reminders of timelines, clarifying any queries and helping to resolve issues that arise during the participant’s progression in the study. At each navigator-participant contact, the participant is informed/ reminded of the requirements for the next step of the study and the associated timeline. Following registration, at each expected, pre-determined point of contact, the treatment navigator attempts to contact the participant for a maximum of three attempts, at least 24 h apart over a 14-day window period.

Furthermore, regardless of any financial incentives offered, all participants are eligible to receive compensatory payments for testing to confirm HCV infection prior to initiation of DAA therapy (AUD 105), and to undergo a test of HCV viral clearance after completion of DAA therapy (AUD 75). Default prescribers, who are not randomised to a co-incentive, are eligible to receive a compensatory payment for each DAA prescription (AUD 50).

### Data management {19}

Data entry, data cleaning, and data management are coordinated by the Health and Clinical Analytics team at the University of Sydney. Data entry is performed by the treatment navigators following relevant training. Data is entered into the previously described project-specific electronic management system and stored in a REDCap platform hosted in a local server.

Documents will be retained and/or disposed per the sponsor’s Research Data Management Policy. In the case of closure of the project, the sponsor will retain an identical replica of the platform database for 15 years or longer, as is required by the approving regulatory authorities. All documentation will be archived until 15 years after the end of the project or publication, whichever is later. Any electronic data recorded on the platform database will also be archived according to the standard procedures of the Sponsor relating to archiving of electronic data.

### Confidentiality {27}

Individual participant data will be held securely by the University of Sydney coordinating centre, as required and permitted by law, and divulged only as necessary to authorised staff directly involved in the project. On all project-specific documents, the participant will be referred to by a unique project number and/or code as in the central database, not by name or other identifying information. Confidentiality agreements are in place between third-party vendors (the SMS-platform provider and the debit card providers) to ensure that personal information and information about the research project will not be disclosed to any unauthorised entity.

### Plans for collection, laboratory evaluation, and storage of biological specimens for genetic or molecular analysis in this trial/future use {33}

N/A. Although the results of routine tests are documented, no laboratory or biological specimens are collected as part of MOTIVATE-C.

## Statistical methods

### Statistical methods for primary and secondary outcomes {20a}

The main statistical objective of MOTIVATE-C is to characterise a dose–response curve where the ‘dose’ corresponds to the allocated incentive value and the ‘response’ corresponds to the propensity to initiate DAA therapy. We characterise superior incentive amounts relative to the notion of a minimum effective dose, which we define as any dose that increases the propensity to initiate DAA therapy by 10 percentage points, in absolute terms, relative to the response on the reference value (AUD 0). We refer to this as the minimum effectiveness criterion.

A Bayesian four-parameter EMAX model will be used to model the dose–response on the log-odds scale, which will be transformed via the inverse link to the probability scale to obtain the posterior probability to initiate DAA therapy at each dose. The EMAX model has been shown to provide good fit for analysing dose–response data and is a pragmatic choice that trades off the need for assumptions versus its flexibility to capture a wide range of dose–response profiles. Sequential analyses will commence once all participants enrolled in first 6 months have reached 12 weeks post-registration. Subsequent analyses are scheduled to occur every 4 months thereafter or after AUD 100,000 is committed as participant incentives, whichever occurs first. At each analysis, we will estimate the propensity to initiate DAA therapy at each incentive value. Inference will be made from Markov chain Monte Carlo (MCMC) draws from the joint posterior.

MOTIVATE-C permits design adaptations as the study progresses that relate to the posterior view of the dose–response curve. We define an effective dose as one which increases the probability of response by more than 10 percentage points in absolute terms relative to the zero-dose response with probability greater than 0.95. We define the minimum effective dose as the lowest incentive value that meets the definition of effectiveness. Any dose for which the probability of effectiveness is less than 0.2 is considered futile. A stopping rule is defined based on futility such that if all incentive values meet the futility definition, then the study will be suspended for review. The other adaptation relates to response-adaptive randomisation, as detailed earlier.

Methods for secondary analyses include logistic and cumulative logit models (assuming proportional odds). An economic analysis will be used to identify an optimal incentive via a cost-effective analysis taking a health services perspective. Cost-effectiveness measures will be summarised as incremental cost-effectiveness ratios and net monetary benefit [15].

All analyses will be undertaken in a Bayesian framework with standard diagnostics run on MCMC chains and using posterior predictive checks for goodness of fit. Additional models may be investigated (and reported as post hoc) as sensitivity and stability checks.

A complete statistical analysis plan will be published separately in accordance with suggested guidelines [16].

### Interim analyses {21b}

Analyses will be conducted at several points over the duration of MOTIVATE-C. Sequential analyses will commence once all participants enrolled in first 6 months have reached 12 weeks post-registration. Based on an expected enrolment rate of two per day and a linear ramp up to this rate over the first 6 months, this equates to approximately 170–200 participants being observed at the first analysis, distributed evenly over the available incentive values. If fewer than 100 participants are available for analysis after 6 months, then the first analysis will be deferred at monthly increments until a minimum of 100 participants have reached 12 weeks post-registration.

Subsequent analyses are scheduled to occur every 4 months thereafter or after AUD 100,000 is committed as participant incentives, whichever occurs first. This rule may be varied as the study approaches exhaustion of awarded funds to ensure all committed funds can be honoured.

The primary analysis will be performed at each analysis and the results will be used to compute the weights for the response-adaptive randomisation. At each analysis there will be some participants who have registered but who have not yet reached 12 weeks follow-up post-registration; these participants will not be included in the current analysis but will be included in subsequent ones. Following each analysis, the results will be used to recompute the weights for the response-adaptive randomisation.

### Methods for additional analyses (e.g. subgroup analyses) {20b}

N/A. No subgroup analyses are planned.

### Methods in analysis to handle protocol non-adherence and any statistical methods to handle missing data {20c}

Missingness is inherent in the study design. Registrants who are insufficiently motivated by the proposed incentive (if any) may choose not to be contacted by a navigator, and participants who fail to initiate therapy with DAA may not contact treatment navigators by 12 weeks post-registration. Navigators will make every reasonable effort to confirm the outcome status of enrolled participants. Failure to enrol or failure to ascertain evidence of successful commencement of DAA therapy by participants will be interpreted as a failure of the intervention.

### Plans to give access to the full protocol, participant-level data, and statistical code {31c}

The ethics-approved full study protocol is available from the authors upon request. De-identified participant level data can be made available after study completion with appropriate ethics approvals. Statistical code can be shared in certain approved cases, subject to the author(s) properly attributing any derived code used for future work.

## Oversight and monitoring

### Composition of the coordinating centre and trial steering committee {5d}

The project steering committee meets quarterly and comprises representatives from the investigator team, independent stakeholders, and community members. The coordinating centre operational team meets every week and comprises project staff involved in the day to day running of the study, including the CPI, project coordinator, software developers, and treatment navigators.

### Composition of the data monitoring committee, its role and reporting structure {21a}

Two independent statisticians, with expertise in clinical research methods and Bayesian statistics, provide independent statistical oversight and monitor adherence to the pre-specified analyses and project decision making processes (as applicable). Details of each analysis will be provided by the study statistician, in confidence, to the statistical monitors for approval.

### Adverse event reporting and harms {22}

It is not anticipated that there will be any significant risk to the safety of participants given the intervention is a payment to the participant (and possibly their nominated prescriber) on commencement of DAA therapy. Nevertheless, when the navigator contacts the participant 2–4 weeks (at the mid-treatment check-in) after initiation of therapy with DAA, all health-related events following treatment initiation will be elicited and documented in the study database. This will be reviewed by the delegated project personnel to assign the seriousness and likely causal relationship of the adverse event to the intervention. We will only report adverse events deemed to be likely causally related to the intervention and occurring within 6 months of participant registration.

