## Introduction

### Background and rationale {6a}

Hepatitis C virus (HCV) infection causes acute and chronic forms of hepatitis. In chronic HCV infection the disease may progress through worsening liver fibrosis to decompensated cirrhosis and/ or hepatocellular carcinoma and the need for liver transplantation [1]. HCV elimination is theoretically achievable thanks to the development of highly effective direct-acting antiviral (DAA) therapies for HCV infection. DAA therapies are associated with a viral cure rate of above 90% regardless of cirrhosis status, with significant improvement in liver function and reduced progression to hepatocellular cancer and end stage liver disease [2, 3]. Compared to older interferon-based therapy, DAA treatment is short (8–12 weeks vs 6–12 months) and has few side effects [4]. In March 2016, Australia became one of the first countries to make DAA therapy broadly accessible to adults with chronic HCV infection. Between March 2016 and December 2022, an estimated 100,684 people living with HCV infection initiated treatment [5]. However, after an initial surge in uptake of DAA therapy, treatment rates have fallen, and an estimated 74,400 Australians remained untreated at the end of 2022 [5].

Pragmatic strategies are needed to ensure people with early-stage chronic HCV infection access DAA therapy to prevent transmission and to avoid the debilitating and costly consequences of late-stage liver disease. Many people with HCV infection are socially marginalized and have difficulty accessing healthcare [5, 6]. Navigation by peers or other support workers has been shown to help people with complex health needs to access and adhere to care, including people with HCV [6].

Direct financial incentives have been shown to be beneficial for improving some desirable health-related behaviours, including vaccine uptake, cessation of smoking, and short-term treatment adherence [7, 8]. However, to date, few studies [9–12] have evaluated the use of financial incentives for short course HCV treatment and there is uncertainty regarding what value of incentives may be required to motivate initiation of DAA therapy. We postulate that a dose–response (incentive vs initiation of therapy) relationship exists and that characterising this relationship is needed to inform the incentivisation of HCV treatment.

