### Participant timeline {13}

The main steps in the participant timeline are (see Table 1):

**Table 1 Tab1:** Study-related events and the associated participant timeline

Events	Time point	Data collected	Type of contact
Registration and randomisation	On Registration – Time 0	Date of registration	SMS interface
Enrolment	As soon as practicable after registration, and not ≥ 12 weeks afterwards	Date of enrolment	Navigator phone/video call
PCR confirmation	As soon as practicable after enrolment, and not ≥ 12 weeks after registration	Evidence and date of HCV RNA PCR testing	Navigator phone/video call
Treatment initiation	As soon as practicable after PCR confirmation, and not ≥ 12 weeks after Registration	Evidence and date of dispensed DAA medication (**Primary outcome**)	Navigator phone/video call
Mid-treatment check-in	14 to 27 days after treatment initiation	Any adverse events (any untoward health-related events)	Navigator phone/video call
End-of-treatment check-in	4–5 weeks after scheduled treatment completion	Participant’s adherence to treatment (number of missed dosages)	SMS-based survey and/or Navigator phone/video call
SVR check	4 to 24 weeks after treatment completion	Evidence and date of SVR result	Navigator phone/video call

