#### Follow-up

Following confirmation that DAA has been dispensed, the participant is informed that they will be contacted in:(i)2–4 weeks following treatment initiation to confirm their receipt of the compensation + / − incentive payment and to document any untoward health-related events, and(ii)4–5 weeks after the expected date of completion of DAA therapy to facilitate a follow-up appointment with their treatment prescriber to test for a viral response (negative HCV PCR at least 28 days after completing therapy). At this end of treatment follow-up, the navigator also confirms and documents the participant’s self-reported adherence to treatment (recalled number of missed days of medication).

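### Adverse events are asked about once, 2–4 weeks after DAA initiation, so the 6-month reporting window is only partly ascertained, and elicited serious events judged unrelated to a payment go unreported

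*Protocol article*

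**What the plan says.** The section 'Adverse event reporting and harms {22}' places the enquiry at the mid-treatment check-in, where "all health-related events following treatment initiation will be elicited and documented in the study database". It continues: "This will be reviewed by the delegated project personnel to assign the seriousness and likely causal relationship of the adverse event to the intervention". Reporting is then restricted: "We will only report adverse events deemed to be likely causally related to the intervention and occurring within 6 months of participant registration". The same section describes the intervention as a payment and anticipates no significant risk from it.

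Three other places agree on a single contact:
- Table 1 ('Participant timeline {13}') lists adverse events in the mid-treatment row only, timed "14 to 27 days after treatment initiation".
- The 'Follow-up' section schedules a contact "2–4 weeks following treatment initiation to confirm their receipt of the compensation + / − incentive payment and to document any untoward health-related events".
- Table 2 gives one timepoint for adverse events: "At the navigator-participant meeting 2–4 weeks following initiation of treatment".

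In Table 1 the two later contacts carry other items. The end-of-treatment check-in collects adherence, and the SVR check collects the PCR result.

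**The concern.** The reporting limit is longer than the described ascertainment. A reader told that no related events occurred within 6 months would reasonably take that period as observed. On the described contacts, most of it would not have been asked about, including at least half of each course of therapy.

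The relatedness restriction is a separate weakness. Events that reach the database pass through a judgement of whether a health event was likely caused by a payment, and only those that pass are reported. Read literally, a serious event attributed to the drug, or to anything else apart from the payment, drops out of the report although it has been collected and graded for seriousness. The trial offers up to AUD 1000 to people whom the protocol describes as often socially marginalised, and its 'Ethical considerations' section answers concern about cash payments from other studies. This trial's own serious events, set out by amount, are what readers will look for.

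**Working it through.** The plan gives no figure to reproduce; the check is timeline arithmetic.

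**Inputs**
- Reporting window: 6 months from registration, taken as 182 days (assumption; 180 to 183 moves the remainders by at most 2 days).
- Initiation day *s*: 0 to 84. Table 1 has "As soon as practicable after PCR confirmation, and not ≥ 12 weeks after Registration", so day 84 is an outer bound and day 83 the last permitted day.
- Adverse event contact *c*: 14 to 28 days after initiation ('Follow-up', Table 2, section {22}); Table 1 stops at 27.
- Course length *L*: 8 to 12 weeks, 56 to 84 days ('Background and rationale {6a}').
- End-of-treatment contact: 28 to 35 days after scheduled completion (Table 1). SVR check: 28 to 168 days after completion (Table 1).
- Initiation proportions: about 15% at baseline, rising by 20 points to 35% ('Sample size {14}').

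**As planned**
1. Day of the only question = *s* + *c*. Earliest 0 + 14 = 14; latest 84 + 28 = 112 (83 + 27 = 110 on Table 1's limits).
2. Window remaining after it: 182 − 14 = 168 days down to 182 − 112 = 70 days.
3. Share of the time from initiation to day 182 that the question covers: 14/182 = 8% at the least, 28/98 = 29% at the most.
4. Share of a full course covered: 8 weeks, 14/56 = 25% to 28/56 = 50%; 12 weeks, 14/84 = 17% to 28/84 = 33%. At least half is never asked about.
5. Latest end of a 12-week course: 84 + 84 = day 168, before day 182. Every course therefore lies inside the window.
6. Only people who start therapy reach this contact. At 15% and 35% initiation, 85% and 65% of those randomised are never asked.

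**With the question added at end of treatment**
1. Contact day = *s* + *L* + 28 to 35: from 0 + 56 + 28 = 84 to 84 + 84 + 35 = 203. It always falls after the end of the course.
2. It does not always reach day 182. On an 8-week course the latest is 84 + 56 + 35 = 175. On a 12-week course it needs *s* of at least 182 − 84 − 35 = 63.
3. For the latest starter on 12 weeks it falls at 12 + 12 + 4 to 5 = week 28–29, beyond the 6-month limit.
4. The SVR contact ranges from 0 + 56 + 28 = day 84 to 84 + 84 + 168 = day 336, so it can cover the remainder for some participants but not for all.

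**Why counts by amount need two denominators**

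Per 100 randomised, 15 people initiate at baseline and 35 at the top of the assumed range. With the same event rate per initiator, the higher amount would show 35/15 = 2.3 times as many events per person randomised.

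**The case against.** The strongest case against is that 6 months is worded as an outer limit on what is reported, not as a promise of active follow-up, so a single contact does not contradict it. That stands. A reader might infer that the protocol breaks a commitment to 6 months of safety observation, or that the window is wholly unobserved. The text supports neither, since the time from initiation to the check-in is covered.

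A reader might also infer that those judging relatedness know the assigned amounts, because the study is open. The document does not establish this. 'Who will be blinded {17a}' says that operational staff other than those it names are not told individual amounts, and section {22} does not say whether the delegated personnel are among them. Nor does it follow that events are lost: all elicited events are documented, and what is restricted is their reporting. This is a condensed article, so the lack of a described route for spontaneous reports does not show that none exists.

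It can be argued that the DAA course is the wrong yardstick, because the intervention is a payment and the check-in also confirms its receipt. This is partly fair. But payment follows sight of the dispensed medication, so observation after payment lasts at most about four weeks and may be much shorter.

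Three practical objections also stand. The end-of-treatment contact may be an SMS survey only. The protocol deliberately collects minimum data from a wary population. A table by amount could mislead without a denominator, because only initiators are asked. These shape the remedy but do not remove the need for it.

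**Conclusion.** The point holds in this form: ascertainment is partial and reporting is selective. One planned question, between day 14 and day 112, leaves 70 to 168 of about 182 days unasked, and at least half of each full course. Elicited serious events judged unrelated to a payment would not be reported.

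This rests on the contacts described in the article, a 182-day window and courses of 8 to 12 weeks completed as scheduled. The consequence is confined to how the safety statement can be read. Randomisation, the adaptation rules and the primary endpoint are not touched, and the protocol itself expects little risk. It is a worthwhile and inexpensive improvement, not a threat to the trial.

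**What to change.** 1. Report all elicited serious events by offered amount whatever their judged relatedness, with relatedness as a column. Give both the number randomised and the number initiating DAA as denominators, and label the table descriptive because only initiators are asked.
2. Put the same adverse event question at the existing end-of-treatment contact, worded so that it works in the SMS survey as well as on a call, and at the SVR call.
3. State the ascertainment period and reconcile the 6-month reporting limit with the contact schedule, so that an event elicited from a late starter at week 28–29 has a defined place.

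The cost is one table and one repeated item at contacts that already exist; no new visits are needed. The downside is a small added burden against the protocol's minimum-data policy. The first step avoids even that, since it uses data already collected.
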